## Abstract

**Background:** Given the limited effectiveness of pharmacological treatments for cognitive decline, non-pharmacological interventions have gained increasing attention. Evidence exists on the effectiveness of cognitive rehabilitation in preventing elderly subjects at risk of cognitive decline and in reducing the progression of functional disability in cognitively impaired individuals. In recent years, telerehabilitation has enabled a broader application of cognitive rehabilitation programs. The purpose of this study is to test a computer-based intervention administered according to two different modalities (at the hospital and at home) using the tools CoRe and HomeCoRe, respectively, in participants with Mild or Major Neurocognitive Disorders.

**Methods:** Non-inferiority, single-blind randomized controlled trial where 40 participants with Mild or Major Neurocognitive Disorders will be assigned to the intervention group who will receive cognitive telerehabilitation through HomeCoRe or to the control group who will receive in-person cognitive intervention through CoRe, with the therapist administering the same computer-based exercises. The rehabilitative program will last 6 weeks, with 3 sessions/week, each lasting ~45 min. All the participants will be evaluated on an exhaustive neuropsychological battery before (T0) and after (T1) the intervention; follow-up visits will be scheduled after 6 (T2) and 12 months (T3).

**Discussion:** The results of this study will inform about the comparability (non-inferiority trial) of HomeCoRe with CoRe. Their equivalence would support the use of HomeCoRe for at distance treatment, favoring the continuity of care.

**Ethics and Dissemination:** This study has been approved by the Local Ethics Committee and registered in https://clinicaltrials.gov (NCT04889560). The dissemination plan includes the scientific community through publication in open-access peer-reviewed scientific journals and presentations at national and international conferences.

**Trial Registration:**
Clinicaltrials.gov
https://clinicaltrials.gov/ct2/show/NCT04889560 (registration date: May 17, 2021).

## Introduction

In the light of the limited efficacy of pharmacological therapies for cognitive decline, the management of modifiable risk factors affecting age-associated cognitive decline and risk of dementia is attracting an increasing interest (1, 2). There is some evidence that early cognitive interventions may be effective in individuals in predementia phases (3, 4). Mild cognitive impairment (MCI) (3) or Mild Neurocognitive Disorder according to the *Diagnostic and Statistical Manual of Mental Disorders-5* (DSM-5) (5) is defined as a transitional status between normal aging and possible development of early dementia. It is characterized by subjective cognitive complaints and objective cognitive decline greater than expected for age and education levels of an individual, but not interfering with activities of daily life. Dementia (i.e., Major Neurocognitive Disorder, according to DSM-5), defined according to severity level, is characterized by multidomain cognitive deficits resulting in a significant interference with independence in everyday activities (5).

In this field of research, previous studies demonstrated the effectiveness of cognitive training programs in patients in the early stage (i.e., MCI and mild dementia) of cognitive decline (6, 7). Traditionally, cognitive interventions consist of in-person sessions usually administered in the hospital setting under supervision by a therapist using paper-and-pencil techniques or technology-based solutions. In particular, the use of technology promotes the development of *ad-hoc* (i.e., user tailored) cognitive rehabilitation tools, allowing to overcome the limits associated to paper-and-pencil techniques. Recent advances in technologies allow for a new and innovative implementation of treatments [i.e., telerehabilitation (TR)], which can be easily diffused on large scale and guarantee a continuum of care at distance (4, 8).

Despite the interesting potentialities of TR, several issues are slowing its integration into the clinical routine. A major issue is the poor technological skills of older adults, which may result in difficulties in managing technological devices autonomously (9). Therefore, platforms should be accessible and user-friendly; duration and frequency of rehabilitation activities should vary according to characteristics of the patients (10); therapists should monitor adherence to treatment and outcome of the rehabilitation process remotely (11). There is some evidence (12–17) exploring the usability and acceptability of Information and Communication Technologies (ICTs) in elderly care including participants with dementia or MCI and giving some recommendations for designing interfaces for this kind of users. In general, it resulted that these systems were enjoyable and feasible for participants even if usability not always was high.

However, randomized controlled trials (RCTs) investigating TR efficacy compared to the traditional in-person approaches are still scanty (4). Recently, this topic has gained growing interest, due to the challenges faced by the healthcare systems during coronavirus disease 2019 (COVID-19) pandemic (18–22).

During the past years, we implemented the software CoRe for in-person cognitive training in the hospital setting supervised by a trainer (23, 24). CoRe has been successfully tested in terms of usability and immediate and long-term effectiveness in participants with early cognitive decline (25–27). In light of the improvement in telemedicine approaches and in view of the willingness of treated participants and caregivers to start/continue CoRe program at distance (28), we have developed the “home” version of CoRe (i.e., HomeCoRe) supporting cognitive intervention remotely (29) with the assistance of a family caregiver.

This longitudinal RCT study, thus, aims to evaluate and compare the effectiveness of HomeCoRe and CoRe programs in participants with MCI or mild dementia. Our hypothesis is that cognitive TR delivered via HomeCoRe provides benefits that are comparable to the in-person version of the program on cognitive and behavioral functioning and on additional participant-centered outcomes.

We are currently performing a small-scale usability test on the HomeCoRe system with encouraging results. The first six participants who completed the usability test considered the HomeCoRe system as an innovative and original tool that they integrated smoothly and positively in their daily life routine. These participants are providing us crucial feedback to improve the system usability such as the need of extra time for performing exercises. Based on the feedback received, HomeCoRe is undergoing a refinement process that will lead to the final version to be used in the RCT.

## Methods and Analysis

### Study Design

This study is a prospective single-blind randomized controlled non-inferiority trial. The Consolidated Standards of Reporting Trials (CONSORT) flowchart for enrollment and randomization is shown in Figure 1. After recruitment, participants will be contacted and will undergo in-person baseline assessment (T0) using the below-listed tests (see evaluation of the participants section and Table 1). Participants who meet the inclusion criteria will be enrolled and randomized to one of two groups: HomeCoRe and CoRe. For both the groups, the intervention will consist of a 6-week program (3 sessions/week, each lasting ~45 min). Follow-up in-person neuropsychological assessments will be scheduled at the end of the rehabilitation program (T1) and after 6 (T2) and 12 months (T3).

**Figure 1 F1:**
[figure not shown]
The Consolidated Standards of Reporting Trials (CONSORT) flowchart for enrollment and randomization.

**Table 1 T1:** Evaluation battery across testing sessions.

	**T0**	**T1**	**T2**	**T3**
**Neuropsycological assessment**				
* **Global cognition** *				
Mini-Mental State Examination (MMSE)	x^*^	x^*^	x	x
Montreal Cognitive Assessment (MoCA)	x	x	x	x
* **Episodic long-term memory** *				
Logical Memory Test immediate and delayed recall	x	x	x	x
Rey's 15 words test immediate and delayed recall	x	x	x	x
Rey Complex Figure delayed recall	x	x	x	x
* **Logical-executive functions** *				
Rey Complex Figure copy	x	x	x	x
Raven's Matrices 1947	x	x	x	x
Frontal Assessment Battery (FAB)	x	x	x	x
Semantic fluency	x	x	x	x
Phonological fluency (FAS)	x	x	x	x
* **Working memory** *				
Verbal Span	x	x	x	x
Digit Span	x	x	x	x
Corsi's block-tapping test span	x	x	x	x
* **Attention/processing speed** *				
Attentive matrices	x	x	x	x
Trail Making Test A and B (TMT)	x	x	x	x
**Questionnaires and scales**				
* **Functional level** *				
Activities of Daily Living (ADL)	x			x
Instrumental Activities of Daily Living (IADL)	x			x
* **Depressive symptoms** *				
Beck Depression Inventory (BDI)	x	x	x	x
* **Health status** *				
36-Item Short Form Health Survey questionnaire (SF-36)	x	x	x	x
* **Cognitive reserve** *				
Cognitive Reserve Index questionnaire (CRIq)	x			
* **Caregiver distress** *				
Caregiver Burden Inventory (CBI)^+^	x	x		
**Participant-centered outcomes**				
* **Impression of symptom change** *				
Patient Global Impression of Change (PGIC)		x		
* **Treatment adherence** *				
Number of sessions carried out		x		

*T0, baseline assessment; T1, post-intervention assessment; T2, 6-month follow-up; T3, 12-month follow-up*.

*
*Is used for the primary outcome,*

+ *is used only for caregivers of participants with Major Neurocognitive Disorder*.

#### Data Collection

Assessments will take place at the Scientific Institute for Research, Hospitalization, and Healthcare (IRCCS) Mondino Foundation (Pavia, Italy). Neuropsychologists carrying out evaluations will receive appropriate instruction and guidance regarding all the assessment procedures and outcome parameters. Reminders (e.g., written reminder, phone calls, and email message) for each visit will be given to all the participants. Research staff collecting data will be blind to group allocation. Not all the outcome measures will be administered at each time point (Table 1).

#### Data Management

Study data will be recorded in the database in processes compliant with the General Data Protection Regulation (GDPR). All the participants will be registered with an identification code. The database will be kept updated to reflect the status of the participant at each stage during the course of this study. The collected data, after scientific publication, will be deposited in dedicated repositories (e.g., Zenodo) according to the good practice of data sharing.

### Participants and Eligibility Criteria

Participants will be recruited from the Dementia Research Center outpatient services and Neurorehabilitation Unit of the IRCCS Mondino Foundation (Pavia, Italy) and screened for eligibility criteria through a clinician evaluation made by an expert neurologist.

The inclusion criteria for participants will be:

Diagnosis of Mild or Major Neurocognitive Disorders based on the DSM-5 (5)Aged between 60 and 85 yearsYears of education ≥ 5Clinical Dementia Rating (CDR) (30) score = 0.5–1.

The exclusion criteria will be:

Mini-Mental State Examination (MMSE) score <20Presence of cognitive impairment secondary to an acute or general medical disorder (e.g., brain trauma or tumor)Presence of severe neuropsychiatric conditions (e.g., mood and behavioral disorders)Presence of severe sensory disorder (e.g., deafness or blindness) or motor impairment that prevent trunk control and/or sitting positionCurrent cognitive treatmentsLack of family support for participants with Major Neurocognitive Disorder

Medication intake for dementia and/or past cognitive rehabilitation treatments will be not considered as exclusion criteria given that these factors are not expected to affect the outcome of this study. Any pharmacological treatment ongoing must be stable across the entire period of this study protocol.

### Evaluation of the Participants

Table 1 lists the evaluation battery (neuropsychological assessment, questionnaires and scale, and participant-centered outcomes) across testing sessions. Each evaluating session would last about 90 min per participant and will be carried out in a hospital setting.

#### Neuropsychological Assessment

The cognitive assessment, performed by using neuropsychological tests standardized for the Italian population, will evaluate the following cognitive domains:

Global cognition:° Mini-Mental State Examination (31)° Montreal Cognitive Assessment (31, 32)Episodic long-term memory: ° Logical Memory Test for immediate and delayed recall (33, 34)° Rey's 15 words test for immediate and delayed recall (35)° Rey Complex Figure delayed recall (36)Logical-executive functions:° Raven's Matrices 1947 (35)° Frontal Assessment Battery (37)° Semantic fluency (33)° Phonological fluency (FAS) (35)° Rey Complex Figure copy (36)Working memory:° Verbal Span (34)° Digit Span (34)° Corsi block-tapping test span (34)Attention/processing speed:° Attentive Matrices (34)° Trail Making Test A and B (38).

Parallel forms (i.e., alternative versions using similar material) will be applied for follow-up visits when available in order to avoid the learning effect. All the test scores will be corrected for age, sex, and education by using appropriate correction grids and compared with the values available for the Italian population.

#### Questionnaires and Scales

Additionally, we will administer questionnaires and scales reported below to evaluate the following aspects:

Functional level:° Activities of Daily Living (39)° Instrumental Activities of Daily Living (39)Depressive symptoms:° Beck Depression Inventory (40)Health status:° 36-item Short Form Health Survey questionnaire (41)Cognitive reserve:° Cognitive Reserve Index questionnaire (42)Caregiver distress:° Caregiver Burden Inventory (43) only for caregivers of participants with Major Neurocognitive Disorder.

#### Participant-Centered Outcomes

In order to assess subjective evaluation of TR success, we will evaluate the following aspects:

Impression of symptom change:° Patient Global Impression of Change (44)Treatment adherence:° Number of sessions carried out.

### Randomization and Stratification

After baseline assessment, we will generate random numbers through the use of a computer algorithm (https://www.random.org/) from a uniform distribution in the range 0–1, dividing the range in two equal intervals and assigning each participant to the group corresponding to the sampled number (1:1 ratio), within strata defined by diagnosis (Mild or Major Neurocognitive Disorders). Neuropsychologists carrying out cognitive evaluations will be blinded to group allocation.

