### Statistical Analysis

#### Sample Size Calculation

Sample size has been estimated based on previous evidence in the literature (47). Since this is a non-inferiority study, we will consider as margin *d* a value of two points difference (T1 vs. T0) at the MMSE between the two groups. We predict to obtain a mean difference between HomeCoRe and CoRe groups of about one point at the MMSE with an SD of 1. Considering an alpha significance of 0.05 and a power of 0.9, the sample size for a non-inferiority study is 18 participants per group, for a total of 36 participants. It is planned to enroll a total of 40 participants in order to account for possible dropouts. If dropout rates between T0 and T1 will be higher than expected, extra participants will be recruited. The sample size for non-inferiority studies was calculated using R 4.0.2 software, SampleSize4ClinicalTrials package.

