#### Planned Analysis

Statistical analysis on outcome measures will be conducted using the SPSS software (see Supplementary Materials for planned analysis). A normality test will be used to assess the distribution of all the outcome measures. Baseline differences between groups will then be tested using the independent samples *t*-test for parametric data and the Mann–Whitney *U*-test for non-parametric data. Within-group statistical tests will be performed for both the CoRe and HomeCoRe groups to look for significant changes in primary and secondary outcome measures over time. Between-group tests will be performed to look for differences in primary and secondary outcome measures between HomeCoRe and CoRe participants. Possible between-group differences in demographic and clinical characteristics (e.g., age, sex, years of education, diagnosis, and cognitive reserve) and in T0 scores in primary and secondary outcome measures will be considered as possible confounders and will be treated as covariates in the analysis. *p* ≤ 0.05, corrected for multiple comparisons, if appropriate, will be considered as statistically significant.

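### The described draw is simple randomisation, so stratifying by diagnosis does not balance Mild and Major disorder, and the 1:1 ratio holds only in expectation

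*Protocol article*

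**What the plan says.** Under Randomization and Stratification, the Protocol article draws random numbers "from a uniform distribution in the range 0–1, dividing the range in two equal intervals", and then proceeds by "assigning each participant to the group corresponding to the sampled number (1:1 ratio), within strata defined by diagnosis". The strata are Mild and Major Neurocognitive Disorder. The section names no block, permuted list, urn, minimisation or cap on counts.

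Under Sample Size Calculation, "the sample size for a non-inferiority study is 18 participants per group, for a total of 36 participants". The allowance for losses follows: "It is planned to enroll a total of 40 participants in order to account for possible dropouts".

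Under Planned Analysis, between-group differences in demographic and clinical characteristics, with diagnosis among the examples, and in baseline scores "will be considered as possible confounders and will be treated as covariates in the analysis".

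**The concern.** Stratification balances a factor only if allocation within each stratum is restricted, so that earlier assignments constrain later ones. Here no draw depends on any earlier one. The section therefore promises balance on diagnosis that its method cannot deliver, and a reader will credit the trial with a protection it lacks.

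The sample size section counts participants per group as if the arms will be about equal. With 40 participants in two strata, chance alone can produce sizeable departures, both in arm sizes and in the mix of diagnoses. If change on the MMSE differs by diagnosis, an uneven mix moves the unadjusted difference between arms. The plan has only 1 point between its expected difference and its margin.

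**Working it through.** **Inputs from the Protocol article.** Probability 0.5 per draw; 40 enrolled; 18 per group required. Margin 2: "we will consider as margin *d* a value of two points difference (T1 vs. T0) at the MMSE between the two groups". Difference 1 and SD 1: "mean difference between HomeCoRe and CoRe groups of about one point at the MMSE with an SD of 1". Error rates: "Considering an alpha significance of 0.05 and a power of 0.9". Sidedness is not stated.

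**Assumption.** The article gives no stratum sizes. I take 10 to 20 of the 40 as having Major disorder.

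**1. The plan's own figure.** n per group = 2·SD²·(z₁₋α + z₁₋β)² / (margin − difference)² = 2 × 1 × (1.645 + 1.282)² / (2 − 1)² = 17.13, rounded up to 18. This reproduces the plan with a one-sided 0.05. A one-sided 0.025 gives 21.01, hence 22, and does not.

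**2. The strata have no effect.** Each assignment is Bernoulli(0.5), independent of all others. The count in one arm is Binomial(m, 0.5) in a stratum of m, and Binomial(40, 0.5) overall. Both hold whether or not the draws are labelled by stratum.

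**3. Arm sizes, X ~ Binomial(40, 0.5).**
- P(X = 20) = C(40,20)/2⁴⁰ = 12.5%.
- P(an arm below 18) = 1 − P(18 ≤ X ≤ 22) = 1 − (0.1031 + 0.1194 + 0.1254 + 0.1194 + 0.1031) = 43.0%, before any dropout.
- P(16:24 or worse) = 26.8%; P(14:26 or worse) = 8.1%.

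**4. Mix of diagnoses.** With M Major participants, let a ~ Binomial(M, 0.5) and b ~ Binomial(40 − M, 0.5) be the Major and Mild counts in one arm. The difference in Major share is |a/(a+b) − (M−a)/(40−a−b)|. Exact enumeration, with ties at 0.20 counted:

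| Major of 40 (assumed) | P(difference ≥ 20 points) | P(difference ≥ 30 points) |
|---|---|---|
| 10 | 17.4% | 3.5% |
| 12 | 18.7% | 4.5% |
| 15 | 20.9% | 5.7% |
| 20 | 26.8% | 8.1% |

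**5. Power.** Normal approximation, all 40 analysed, one-sided 0.05: power = Φ(1/√(1/n₁ + 1/n₂) − 1.645).

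| Split | Power |
|---|---|
| 20:20 | Φ(3.162 − 1.645) = 93.5% |
| 17:23 | Φ(3.126 − 1.645) = 93.1% |
| 14:26 | Φ(3.017 − 1.645) = 91.5% |
| 12:28 | Φ(2.898 − 1.645) = 89.5% |

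Averaged over Binomial(40, 0.5), power is 93.0%. A split of 12:28 or worse, where power is below 90%, has probability 1.7%. With only 36 evaluable and a t-test, power is 0.902 for equal arms and 0.894 averaged over binomial splits.

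**6. Under a restricted scheme.** With permuted blocks of 4 within each diagnosis (illustrative), the arms differ by at most 2 per stratum and 4 overall. The worst split of 40 is 18:22 (power 93.3%). For 10 to 20 Major participants, the largest possible difference in Major share is 10 points.

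**The case against.** The strongest reply is that simple randomisation is a valid method. It gives an unbiased comparison, ordinary standard errors already allow for chance imbalance, and its draws cannot be predicted. The 18 per group is a calculation for equal arms, not a floor for each arm, and a 17:23 split costs only 0.4 percentage points of power. The Planned Analysis also names diagnosis as a possible covariate. All of this stands, and it limits the size of the point. It does not rescue the stratification, which remains without effect. The adjustment is also tied to differences found between the arms, so whether diagnosis enters the primary model depends on the data.

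A reader might go further in three ways that the article does not support.

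- **Weak concealment, or room to redraw.** The article does not say whether numbers are drawn one at a time, by whom, or how assignments are released. An article may leave these details to the full protocol. Independent draws also make the next assignment unpredictable.
- **Diagnosis chosen because it drives prognosis.** The article gives no reason for the choice.
- **A large shift in the estimate.** The shift is the gap in MMSE change between diagnoses multiplied by the imbalance in share. At a 20-point imbalance, assumed gaps of 0.5 to 2 points give 0.5 × 0.20 = 0.1 to 2 × 0.20 = 0.4 points, unadjusted. The upper end fits poorly with the plan's SD of 1. A 2-point gap alone contributes variance 4p(1 − p), where p is the Major share: 0.75 at 10 of 40, 0.94 at 15 and 1.00 at 20, out of a total variance of 1.

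**Conclusion.** The point holds as a fault in the stated procedure. Stratification by diagnosis has no balancing effect as written, and 1:1 sets the draw probability without securing equal arms. The 43.0% and 12.5% are exact for 40 randomised. The 17% to 27% chance of a 20-point gap in Major share rests on the assumed stratum sizes.

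The harm is lost balance and some precision, not bias or a material loss of power. It should be fixed, but it does not by itself undermine the trial. If a restricted scheme is in fact in use, the fault lies only in the description.

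**What to change.** - **Allocation.** Replace the independent draw with permuted blocks of randomly varying, concealed size within each diagnosis stratum. If a restricted scheme is already used, correct the Randomization and Stratification text to describe it.
- **Analysis.** Name diagnosis as a fixed covariate in the primary MMSE analysis, whatever imbalance is observed.

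The cost is small: generating a list with ordinary software, and one model term stated in advance. The drawback is that assignments near the end of a block become slightly more predictable, which varying the block sizes limits.
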